#### Secondary Outcomes

A trained physician measured forced expiratory volume in the first second (FEV1), forced vital capacity (FVC), and the FEV1/FVC ratio using a portable spirometer (Easy-On-PC). These spirometers are frequently used in pulmonary research because their calibration remains stable over time [23]. We aimed to obtain at least three acceptable and two reproducible tests following joint recommendations of the American Thoracic Society and European Respiratory Societies [24] or until the participant was no longer able to tolerate the procedure. Results were recorded on a secure interface (EasyOnConnect) on a personal computer.

For mental health and QoL assessments, participants responded to questionnaires administered by a trained health worker. We used PHQ-9, GAD-7, and IES-R questionnaires to assess mental health, including depression [25], anxiety [26], and posttraumatic stress disorder symptoms [27], respectively. Mental health questionnaires were administered at 2, 4, 7, 8, and 12 weeks after hospitalization by telephone home calls. We used the SF-36 v2 [28] and EQ-5D [29] questionnaires to measure QoL at 7 and 12 weeks after discharge. The psychometric properties of the SF-36 questionnaire have been widely studied and consist of 36 items assessing 8 dimensions: physical functioning, physical role, bodily pain, general health, vitality, social functioning, emotional role, and mental health [30]. The details of the measurements for the primary and secondary outcomes are summarized in Table 3. We used the SGRQ to assess respiratory symptoms, an instrument recommended to measure changes in respiratory health following interventions [31]. We measured respiratory symptoms at 7 and 12 weeks after hospital discharge (Table 1).

**Table 3 table3:** Outcomes and instruments in the WAYRA study.

Outcome	Instruments
Pulmonary function	6-minute walk test, spirometry [20]
Respiratory symptoms	St. George’s Respiratory Questionnaire (SGRQ) [31]
Depressive symptoms	Patient Health Questionnaire (PHQ-9) [25]
Anxiety symptoms	Generalized Anxiety Disorder (GAD-7) [26]
Posttraumatic stress disorder	Impact Event Scale-Revised (IES-R) [27]
Quality of life	36-Item Short-Form Health Survey [28], EuroQol-5D (EQ-5D) [29]

### Statistical Analyses

We will perform an intention-to-treat analysis of primary and secondary outcomes at 7 and 12 weeks after hospital discharge. The final analysis will be performed when all 108 participants completed the trial. We will compare the 6MWD (meters), FVC (liters), FEV1 (liters), and questionnaire scores at 7 and 12 weeks after hospitalization discharge between the intervention and control arms. In the secondary analyses, we will compare the proportion of participants with respect to restrictive spirometry pattern, depression, anxiety, and posttraumatic stress disorder at 7 and 12 weeks after hospital discharge between the intervention and control arms. In addition, following the recommendation by Cocks and Torgerson [32], we will use a one-sided 80% CI to determine if this trial should proceed to a phase III trial. As a sensitivity analysis, the association between the number of therapies received and outcomes will be examined, adjusting for potential confounders that will be identified by a causal acyclic diagram. There will be no formal interim analysis of the data.

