**Methods:**

WAYRA (the word for air in the Quechua language) was an open-label, unblinded, two-arm randomized controlled trial. We recruited 108 participants aged 18-75 years who were discharged from the hospital after COVID-19 pneumonia that required >6 liters/minute of supplemental oxygen during treatment. Participants were randomly assigned at a 1:1 ratio to receive the combined rehabilitation program or usual posthospital care provided by a public Peruvian hospital. The intervention consisted of 12 at-home respiratory rehabilitation sessions and 6 telephone-based psychological sessions. The primary outcome was the 6-minute walk distance. Secondary outcomes included lung function, mental health status (depression, anxiety, and trauma), and quality of life. Outcomes were assessed at baseline (before randomization) and at 7 and 12 weeks after hospital discharge to assess the difference between arms.

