### Study Setting and Population

This study took place in the COVID-19 ward at Hospital Nacional Cayetano Heredia (HNCH), a public tertiary-care hospital and a major referral center that serves approximately 3 million people from underserved neighborhoods in the northern metropolitan area of Lima, the capital of Peru. HNCH has been one of the main COVID-19 national referral centers throughout the pandemic, with 241 hospitalization beds and 23 intensive care unit beds [14]. During the pandemic, more than half of Lima’s population reported depressive symptoms, with increased rates of symptoms reported among young people with low income and without higher education [15].

The study population consisted of confirmed cases of COVID-19, diagnosed by serological or molecular tests, including members of both sexes, between 18 and 75 years of age, discharged from hospitalization, who received high-flow oxygen (>6 liters/minute) treatment at any point during hospitalization. Participants with prior respiratory pathology or psychiatric diagnoses were excluded. The complete eligibility criteria are provided in Textbox 1.

Inclusion and exclusion criteria.

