### Randomization

We used a blinded list preuploaded in REDcap [17], which was created by a data administrator who was not involved in study recruitment. To achieve balance in the number of participants assigned to each study arm, the treatment arm was randomized at a 1:1 ratio using permuted blocks of variable size, randomly varying from 2, 4, and 6 participants. The blocks were randomized using the Stata v16.0 *ralloc* command (StataCorp). Finally, all participants were scheduled for follow-up visits as described in Table 1. Sample selection and enrollment took place between the day before hospital discharge and up to 3 days after discharge.

**Table 1 table1:** Data collection schedule.

Time point				Study period (week)																											
				Enrollment (–1)		Baseline (0)		Postallocation																							Close-out (12)
								1		2		3		4		5		6		7		8		9		10		11			

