	**Secondary outcomes**																														
		Spirometry^b^			✓														✓										✓		
		Respiratory symptoms (SGRQ^c^)			✓														✓										✓		
		Quality of life (SF-36^d^, EQ-5D^e^)			✓														✓										✓		
		Mental health (PHQ-9^f^, GAD-7^g^, IES-R^h^)			✓				✓				✓						✓		✓								✓		
		Cognitive function (MoCA-BLIND^i,^ visual impairment)			✓				✓				✓						✓		✓								✓		

^a^6MWT: 6-minute walk test.

^b^Includes forced expiratory volume in 1 second (FEV1), forced vital capacity (FVC), and FEV1/FVC ratio.

^c^SGRQ: Saint George’s Respiratory Questionnaire.

^d^SF-36: 36-Item Short Form Survey.

^e^EQ-5D: EuroQuol 5D.

^f^PHQ-9: Nine-Item Patient Health Questionnaire.

^g^GAD-7: Generalized Anxiety and Depression.

^h^IES-R: Impact of Event Scale-Revised.

^i^MoCA-BLIND: Montreal Cognitive Assessment visual impairment version.

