### Measured Outcomes

#### Primary Outcome

The primary health outcome was the change in 6-minute walk distance (6MWD) at 7 and 12 weeks after discharge compared to baseline. The 6MWT is a submaximal effort test of cardiorespiratory functional capacity with correlation to QoL and independence in activities of daily living [20]. The 6MWT is widely used for the follow-up of patients after hospitalization because patients can self-regulate the intensity of the activity, resting as often as desired, leading to minimal risks of adverse events during the activity [20]. The test was performed in a 20-meter hospital aisle marked according to the recommendations of the American Thoracic Society [21,22]. Participants who demonstrated instability while standing, generalized weakness, or those with a decrease in oxygen saturation below 90% or increased heart rate of >130 beats per minute while standing did not perform the test. In this case, the participants were considered to have covered 0 meters. Each participant only attempted the test once. The number of meters walked in the 6MWT was calculated by the assessor and recorded in the data collection form.

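### FVC and FEV1 are set to be compared as follow-up litres, with no stated use of baseline spirometry or size standardisation; this costs precision but adds no bias

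*Protocol article*

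**What the plan says.** The Statistical Analyses section of the protocol article fixes both the unit and the contrast: "We will compare the 6MWD (meters), FVC (liters), FEV1 (liters), and questionnaire scores at 7 and 12 weeks after hospitalization discharge", intervention against control. The next sentence adds a binary spirometry outcome: "we will compare the proportion of participants with respect to restrictive spirometry pattern". That pattern is not defined, and no reference equation, predicted value or lower limit of normal is named anywhere.

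Three other statements bear on the point:

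- Study Setting and Population describes the sample as "including members of both sexes, between 18 and 75 years of age".
- Under Randomization, "the treatment arm was randomized at a 1:1 ratio using permuted blocks of variable size"; no stratification factor is mentioned.
- The abstract states "Outcomes were assessed at baseline (before randomization) and at 7 and 12 weeks after hospital discharge". The Enrollment section and Table 1 confirm that spirometry is among the baseline measurements.

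A baseline-referenced form is given for one outcome only: "The primary health outcome was the change in 6-minute walk distance (6MWD) at 7 and 12 weeks after discharge compared to baseline". Covariate adjustment appears only in the sensitivity analysis of the number of therapies received.

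**The concern.** Lung volume in litres depends on height, sex and age, which is why prediction equations use them. In a mixed-sex sample spanning 57 years of age, a follow-up value in litres therefore varies between people for reasons unrelated to recovery from pneumonia. That variation goes straight into the standard error unless it is removed by standardising for size or by using each participant's own baseline value.

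The sentence in the article does neither, although one remedy is already in the data set and the other probably is, since classifying a restrictive pattern ordinarily needs a predicted value or lower limit. At stake is whether a trial of about 43 evaluable participants per arm can say anything useful about lung function, which is among the outcomes the programme aims to improve.

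**Working it through.** **Number per arm.** The Sample Size Calculation section gives 86 evaluable participants, inflated for 20% loss: 86 / 0.8 = 107.5, rounded up to 108, which matches the stated total. So n = 86 / 2 = 43 per arm. That calculation concerns the walk distance; the article gives no SD, effect or power for FVC or FEV1.

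**Assumptions, none from the documents.** Raw between-person SD of FVC: 0.7 to 1.0 L. Share of variance explained by sex, age and height (R²): 0.5 to 0.7, with 0.3 as a pessimistic case. Correlation of baseline with follow-up FVC (ρ): 0.7 to 0.9, with 0.6 as a pessimistic case. Two-sided alpha 0.05.

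**Formulas.**

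- Standard error of the arm difference = SD × √(2/43) = SD × 0.2157.
- Difference detectable with 80% power = (1.960 + 0.842) × SD × 0.2157 = 0.604 × SD.
- Residual SD after size standardisation = SD × √(1 − R²).
- Residual SD after baseline adjustment = SD × √(1 − ρ²).

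The last column takes, as an example, a raw SD of 0.9 L and a true difference of 0.3 L.

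| Analysis | SD multiplier | Detectable difference, SD 0.7 to 1.0 L | Reduction | Power, example |
|---|---|---|---|---|
| Follow-up litres, unadjusted | 1.000 | 0.42 to 0.60 L | none | 34% |
| Size removed, R² = 0.3 | 0.837 | 0.35 to 0.51 L | 16% | 46% |
| Size removed, R² = 0.5 | 0.707 | 0.30 to 0.43 L | 29% | 59% |
| Size removed, R² = 0.7 | 0.548 | 0.23 to 0.33 L | 45% | 81% |
| Baseline-adjusted, ρ = 0.6 | 0.800 | 0.34 to 0.48 L | 20% | 49% |
| Baseline-adjusted, ρ = 0.7 | 0.714 | 0.30 to 0.43 L | 29% | 58% |
| Baseline-adjusted, ρ = 0.8 | 0.600 | 0.25 to 0.36 L | 40% | 73% |
| Baseline-adjusted, ρ = 0.9 | 0.436 | 0.18 to 0.26 L | 56% | 94% |

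The percentage reduction does not depend on the assumed raw SD, only on R² or ρ. The two gains do not add up, because both remove largely the same variation between people.

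**Chance imbalance in sex.** Assume 60% men and a male-female gap of 1.2 L. The standard error of the difference in proportion male is √(2 × 0.6 × 0.4 / 43) = 0.106, so an imbalance of one standard error shifts FVC by 0.106 × 1.2 = 0.13 L. With a raw SD of 0.95 L, the standard error of the arm difference is 0.95 × 0.2157 = 0.205 L, and the 95% half-width is 1.99 × 0.205 = 0.41 L. The 0.13 L is a component of that 0.205 L, not an addition to it.

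**The case against.** The strongest reply is that the sentence lists outcomes and units and does not specify a model. It names no test and does not say that the comparison is unadjusted. It also lists the walk distance as a value at each visit, although that outcome is defined elsewhere as a change from baseline, so it may be shorthand throughout. A covariate model commonly sits in a full protocol or analysis plan, and neither is shown. This stands in part: the absence of a model is no fault of the article. But litres at follow-up are a stated choice, and for spirometry, unlike the walk distance, no other section supplies a baseline-referenced definition.

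Several stronger readings are tempting, and the documents do not support them:

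- That body size, sex and age overwhelm any treatment effect. With no SD, expected effect or variance share for FVC or FEV1, this cannot be shown.
- That chance imbalance in sex or height makes a false finding more likely. Under 1:1 randomisation the comparison in litres is unbiased, and its standard error already allows for such imbalance, as the working shows.
- That reference values are indispensable, or certainly already computed. Baseline-adjusted litres do as well or better over much of the assumed range, and the existence of predicted values is only inferred from an undefined restrictive pattern.

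**Conclusion.** The point holds as one of efficiency. Followed as written, the comparison leaves removable between-person variance in the error term. Under the assumptions above, the detectable difference could be smaller by about 29 to 45% with size standardisation and 29 to 56% with baseline adjustment. In the pessimistic cases the gain is 16 to 20%, which matters because baseline was measured around hospital discharge, when values may track later ones less closely than in stable people. The direction is general; the size rests on figures the documents do not contain.

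The effect is on precision, not on bias or the false-positive rate. It concerns secondary outcomes for which the trial was not sized. The change is worth making because it costs little, but the primary result does not depend on it.

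**What to change.** Compare FVC and FEV1 between arms at weeks 7 and 12 by analysis of covariance with the participant's baseline value as covariate. Use litres or, preferably, percent-predicted or z-scores. Name the reference equation and use the same one to define the restrictive pattern. Keep unadjusted litres as a descriptive summary.

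Analysis of covariance is preferable to a simple change score: in the example above at ρ = 0.7, power is 58% against 51% for change, whose SD multiplier is √(2 − 2ρ) = 0.775.

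The cost is a sentence or two in the analysis plan. No new measurement is needed for the baseline-adjusted version. The standardised version also needs height, which the article does not list by name but which classifying a restrictive pattern would ordinarily require. The downsides are some dependence on the chosen reference equation and the need for a rule for participants without an acceptable baseline test.

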## Introduction

The COVID-19 pandemic is resulting in millions of survivors with long-term complications [1]. Complications are more frequent in patients who required hospitalization, affecting both physical and mental health [1]. Systematic reviews show that 24% to 36% and 40% to 58% of patients with COVID-19 report dyspnea and fatigue after acute illness, respectively [2,3]. The frequency of depression and anxiety in COVID-19 survivors ranges from 12% to 15% and 13% to 22%, respectively [2-5].

Although recommendations for post-COVID-19 rehabilitation already exist [6-9], the evidence is scarce from different aspects. First, most studies have focused on pulmonary rehabilitation [10-12], but no study has evaluated a rehabilitation program that integrates a psychological component. The high frequency of mental illness suggests that patients may benefit from physiological support. Second, no published clinical trial has evaluated a home-based rehabilitation program, an approach that could have advantages over inpatient programs and comparable efficacy [12]. After hospitalization, COVID-19 patients could have several health limitations that make it difficult to visit health care facilities for rehabilitation. Third, most strategies to address the sequelae of COVID-19 have been developed in high-income countries and therefore do not consider some of the challenges specific to developing countries, such as the availability and quality of professionals and infrastructure to carry out rehabilitation [13].

Considering that COVID-19 is a disease that results in short-, medium-, and long-term physical and mental impairment, and that limited rehabilitation strategies have been evaluated, this protocol describes the design and methodology of a randomized controlled trial that aimed to evaluate the effects of integrated home-based respiratory physiotherapy combined with a telephone-based psychological intervention on pulmonary and mental health–related outcomes at 7 and 12 weeks after hospital discharge in patients with COVID-19 pneumonia. The primary objective of the trial was to compare 6-minute walking distances at 7 and 12 weeks after hospital discharge among participants in a combined program versus those who received usual posthospital care provided by a Peruvian public hospital.

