### Sample Size Calculation

We used STATA Version 16 (StataCorp) to calculate the ideal sample size. We attempted to enroll 108 participants in total, allocating 54 to each treatment arm. We estimate that a sample size of 86 participants would be sufficient to detect a mean difference between arms of 55.1 meters in the 6MWT according to the study by Liu et al [11] considering a 95% CI and 90% power. Assuming a potential 20% rate of rejection or loss to follow-up, we aimed to achieve a sample of 108 participants.

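### The primary outcome is defined as change in 6-minute walk distance but compared as distance at follow-up, so the primary estimator, and the version to which the 90% power applies, are left open

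*Protocol article*

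**What the plan says.** The outcome definition (Methods, Primary Outcome) is explicit: "The primary health outcome was the change in 6-minute walk distance (6MWD) at 7 and 12 weeks after discharge compared to baseline".

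The analysis (Methods, Statistical Analyses) names a different variable: "We will compare the 6MWD (meters), FVC (liters), FEV1 (liters), and questionnaire scores at 7 and 12 weeks after hospitalization discharge", between the two arms. The word change does not appear there. The primary objective at the end of the Introduction follows the analysis wording rather than the definition: it is to "compare 6-minute walking distances at 7 and 12 weeks after hospital discharge". The Abstract says only "The primary outcome was the 6-minute walk distance", which fits either version.

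The Sample Size Calculation is meant to "detect a mean difference between arms of 55.1 meters in the 6MWT". It does not say whether this is a difference in change or in distance at follow-up, and it gives no SD.

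Three further statements bear on the point:
- Baseline 6MWD is available for adjustment: "Outcomes were assessed at baseline (before randomization) and at 7 and 12 weeks after hospital discharge".
- The one covariate adjustment mentioned, "adjusting for potential confounders that will be identified by a causal acyclic diagram", belongs to the sensitivity analysis of number of therapies received, not to the comparison of arms.
- For participants unable to perform the test, "In this case, the participants were considered to have covered 0 meters".

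**The concern.** A primary outcome should point to one estimator, and here the text points to two. For a given visit they differ by exactly the baseline difference between arms that arose by chance:

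(difference in change) = (difference at follow-up) − (difference at baseline).

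Randomisation is by permuted blocks that balance numbers per arm; no stratification by baseline 6MWD is described. In about 86 evaluable participants, the chance baseline difference need not be small.

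Two things are at stake. First, whoever runs the analysis can report either version and cite the article for it. Second, the stated 90% power, on which the claim of adequate power in Strengths and Limitations relies, may be true of one version only. The 0 m scoring rule could widen the gap in a given sample, because a participant scored 0 m at baseline can show a very large change. How often this happened is not stated.

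**Working it through.** **Inputs from the Sample Size Calculation.** Difference 55.1 m; 90% power; 95% confidence, read as two-sided 5%; 86 evaluable, so 43 per arm; 20% loss; 108 enrolled.

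**Inputs that must be assumed.** The SD, the baseline–follow-up correlation r, and equal variance at baseline and follow-up. None of these is in the article.

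**Step 1: reproduce the plan's figure.** The inflation reproduces: 86 / (1 − 0.20) = 107.5, rounded up to 108, or 54 per arm. The 86 cannot be reproduced forwards without an SD, so I solved for it. By the normal approximation:

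SD = 55.1 × √(43/2) / (1.960 + 1.282) = 78.8 m.

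SDs of 77.9 to 78.8 m all give 43 per arm on that formula; a two-sample t-test calculation gives 77.0 to 77.9 m. I use 77.9 m with the t-test, for which power at 43 per arm is 90.0%.

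**Step 2: SD of each version.** With follow-up SD s and equal variances:
- follow-up distance: s
- change: s × √(2(1 − r))
- baseline-adjusted: s × √(1 − r²)

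Change and follow-up distance are equally precise only at r = 0.5. The adjusted comparison is at least as precise as either at any r, since 1 − r² ≤ 1 and 1 − r² = (1 + r)(1 − r) ≤ 2(1 − r).

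**Step 3a: power if 77.9 m is the SD of follow-up distance.**

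| r | Follow-up distance | Change (SD) | Baseline-adjusted (SD) |
|---|---|---|---|
| 0.3 | 90% | 78% (92.2 m) | 92% (74.3 m) |
| 0.5 | 90% | 90% (77.9 m) | 96% (67.5 m) |
| 0.7 | 90% | 99% (60.3 m) | 99.5% (55.6 m) |

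**Step 3b: power if 77.9 m is the SD of change.** The follow-up SD is then 77.9 / √(2(1 − r)).

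| r | Change | Follow-up distance (SD) | Baseline-adjusted (SD) |
|---|---|---|---|
| 0.3 | 90% | 97% (65.8 m) | 98% (62.8 m) |
| 0.5 | 90% | 90% (77.9 m) | 96% (67.5 m) |
| 0.7 | 90% | 71% (100.6 m) | 94% (71.8 m) |

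Which version falls short depends on r and on which SD lies behind the 86. The article settles neither.

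**Step 4: unequal variances.** If the baseline SD is k times the follow-up SD, the change SD is s × √(1 + k² − 2rk). With s = 78.8 m and the normal approximation, change-score power at r = 0.3, 0.5 and 0.7 is 88%, 95% and 99.5% for k = 0.7, and 65%, 79% and 94% for k = 1.3. The adjusted comparison does not depend on k and has 93%, 96% and 99.5%.

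**Step 5: how far apart the two estimates lie.** If the baseline SD is 77.9 m, the chance baseline difference has an SD of 77.9 × √(2/43) = 16.8 m, and 16.8 / 55.1 = 30% of the target effect. At 54 per arm it is 15.0 m.

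**Step 6: freedom to choose.** In simulation with 43 per arm, no true effect and r from 0.3 to 0.7, at least one of the two versions reached two-sided p < 0.05 in about 9% of trials (8.8% to 9.2%) rather than 5%.

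**The case against.** The strongest reply is that this is a journal article. The sentence in Statistical Analyses may be shorthand for comparing the outcome as already defined, with the model and covariates set out in a full protocol or analysis plan that is not shown. Part of that stands. The Abstract's wording is no contradiction by itself. But the Statistical Analyses section and the stated objective both describe distance at the two visits, and the outcome definition describes change. An unseen document cannot make those agree.

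Four stronger readings are tempting, and the article supports none of them.
- **That the plan has decided against adjusting for baseline.** It names no test, model or covariate for the comparison of arms. That is silence, and such detail is commonly left to the analysis plan.
- **That participants with a missing visit will be dropped.** No such rule is stated. The analysis is called intention-to-treat, and a repeated-measures model would also fit the wording.
- **That the comparison is biased or the sample size wrong.** With randomisation and complete data, both versions have the same expected difference. What is affected is precision, sensitivity to chance imbalance and freedom of choice.
- **That the change score is the underpowered version.** This holds only at lower correlations and if the implied SD belongs to follow-up distance. Otherwise the shortfall can move to follow-up distance.

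It is also fair to say that a single sentence choosing either version would remove the contradiction. Baseline adjustment is recommended because it makes the choice unnecessary and costs no precision.

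**Conclusion.** The contradiction is in the text and needs reconciling: the definition says change, the analysis and objective say distance at follow-up, and the 55.1 m is attached to neither. The primary estimator is therefore open.

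The size can only be illustrated. With the assumed SD of 77.9 m, equal variances, 43 per arm and correlations of 0.3 to 0.7, the version not matching that SD has power from 71% to 99% against the stated 90%. The baseline-adjusted comparison stays at 92% or more throughout. The two unadjusted estimates would typically differ by an amount with an SD near 17 m if the baseline SD is 77.9 m. All of these figures move with the SD and the correlation, which the article does not give. They do not show that the trial is underpowered.

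**What to change.** Before the blinded analyst is unblinded, make these changes and date them:

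1. State one primary analysis in the same words in the Introduction (objective), Primary Outcome and Statistical Analyses: the between-arm difference in 6MWD at follow-up, in metres, adjusted for the 6MWD measured before randomisation. In a linear model containing baseline, the treatment estimate is identical whether the outcome is entered as change or as follow-up distance, so both descriptions are satisfied.
2. In Sample Size Calculation, say which version the 55.1 m refers to, and give the SD used.
3. Use the same approach for the continuous secondary outcomes, each adjusted for its own baseline.

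A repeated-measures model using all available visits is one suitable implementation but is not needed to resolve this point. Adjusting for baseline does not decide how weeks 7 and 12 share the primary role; the text should settle that separately. If any participants have a baseline of 0 m under the scoring rule, check that a linear baseline term describes them adequately.

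The cost is a few sentences and a few lines of analysis code. The schedule already has baseline 6MWD measured, so no new data are needed.
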